### Randomization

An independent statistician prepared the randomization by using computer-generated randomization tables. To prevent unequal randomization, employees are pre-stratified by duration of sick leave (short-term <6 weeks or long-term ≥6 weeks) and whether they are on full-time (100 %) or part-time (≤99 %) sick leave. Block randomization with blocks of four will be applied to ensure equal group sizes within each stratum. A separate block randomization table is generated for each of the four participating vocational rehabilitation centers. For each stratum, the researcher will prepare opaque, sequentially numbered, and sealed coded envelopes, with a note for either the 40-h VR or 100-h VR. After the multidisciplinary screening (at baseline), the multidisciplinary screening team and rehabilitation physician will fulfil all study criteria. If participants meet all criteria, they will be allocated to 40-h or 100-h VR. Treatment allocation will be performed by a member of the multidisciplinary screening team (MST) at each center and can be performed at the center or via telephone (this will differ among the centers). The MST member hands over two envelopes (left over) of that stratum, and the patient is asked to pick one of the envelopes, open the envelope and sign the note. In the case of telephone allocation, the MST member will ask the patient to sign informed consent and to return it via a reply envelope. When the signed informed consent is received, the MST member will perform the treatment allocation without the patient. After randomization, a research assistant will make an appointment for the patient’s first intervention date.

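### Picking one of two leftover envelopes removes the numbered sequence's control over allocation; the telephone route has no stated envelope rule; and fixed blocks of four make some allocations foreseeable

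*Protocol article*

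**What the plan says.** All of this is in the protocol article, section Randomization, unless another section is named.

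- An independent statistician generates the tables by computer. From these the researcher prepares "opaque, sequentially numbered, and sealed coded envelopes" for each stratum.
- "Block randomization with blocks of four will be applied to ensure equal group sizes within each stratum". The strata are sick-leave duration (two levels) and full-time or part-time sick leave (two levels). "A separate block randomization table is generated for each of the four participating vocational rehabilitation centers".
- A member of the local screening team carries out the allocation. In person, "The MST member hands over two envelopes (left over) of that stratum, and the patient is asked to pick one of the envelopes"; the patient then opens it and signs the note.
- By telephone, once the signed consent form has come back, "the MST member will perform the treatment allocation without the patient". No rule is given for choosing the envelope.
- The Blinding section and the limitations in the Discussion say that patients, the intervention team and the screening team cannot be blinded. The primary outcome is self-reported sick leave (Primary outcome).

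**The concern.** Numbered envelopes protect a random sequence only if the next number must be used. Once one of two may be taken, the computer-generated order stops fixing the allocation. An envelope used out of turn is then normal practice and no longer a warning sign. In the telephone route one unblinded person allocates with neither the patient present nor a written rule.

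That person is poorly placed for the task. The screening team assesses the patient, helps apply criteria that include motivation (Study population), and prioritizes the 30 hours of modules for each 40-h patient (40-hour vocational rehabilitation). It is therefore likely to hold a view on who needs the longer programme.

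The fixed block size is a second, independent weakness. In an open trial with small strata it lets an attentive team member foresee some allocations.

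At stake is selection bias in an unblinded, self-reported outcome. If harder cases went to 100-h, the 40-h minus 100-h difference would fall and favour a false claim of non-inferiority. Requiring both intention-to-treat and per-protocol success (Statistical methods) does not protect against this, because both analyses inherit the same allocation. Adjustment for baseline differences reaches only measured factors.

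**Working it through.** **Inputs from the article.** Block size 4, 1:1 allocation; 4 centres × 2 × 2 = 16 cells; N = 174; SD 80 days; margin 30 days; expected difference −8 days; alpha 0.025; power 80 %; 15 % loss; ICC 0.05.

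**The plan's own figure.** Per arm, n = 2 × 80² × (1.96 + 0.84)² / (30 + 8)² ≈ 69.6, so 70. Then 70 × 1.05 = 73.5, so 74, and 74 / 0.85 = 87.06, about 87 per arm, or 174 in total. The figure reproduces if the ICC enters as a factor of 1.05. It is not in dispute here and is used only for scale.

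**Cell size.** 174 / 16 = 10.9 patients, fewer than three blocks of four per cell.

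**Predictability with blocks opened in order.** The observer is assumed to know the block size and the earlier allocations in the cell. There are 6 possible blocks and 24 positions.

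- Certain in advance: the fourth position always (6), and the third when the first two match (2 of 6 blocks). That is 8/24 = 1/3, or 174 / 3 = 58 patients.
- Best-guess success by position: 1/2, 2/3, then (1/3 × 1 + 2/3 × 1/2) = 2/3, then 1. The mean is (1/2 + 2/3 + 2/3 + 1) / 4 = 17/24 = 70.8 %.

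**What a blind pick of two changes.** The article does not say how the two envelopes are assembled or what happens to the one not picked, so two readings were simulated (100,000 runs, 12 patients per cell).

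| Procedure | Patients given an envelope other than the one in order | Best-guess hit rate | Mean imbalance after 12 |
|---|---|---|---|
| Strict number order | 0 % | 70.8 % | 0 |
| Pick of two within a block | 62.5 % | 70.8 % | 0 |
| Pick of two, other envelope carried forward | 73 % | 66.5 % (from running imbalance) | 0.5 |

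The pick leaves predictability unchanged or slightly lower. What it removes is control by the sequence and, under carry-forward, the 2:2 balance in each block. In 4 of the 6 possible blocks the first two envelopes hold different arms, so if concealment failed, whoever chose between them could settle the arm.

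**Scale of a possible bias (illustration, not an estimate).** Suppose k patients, each d days worse than average, all go to 100-h instead of being split evenly. The 100-h mean rises by (k/2) × d/n and the 40-h mean falls by the same amount, so the difference shifts by k × d/n towards 40-h.

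- Standard error: 80 × √(2/87) = 12.1 days; with 74 analysed per arm, 80 × √(2/74) = 13.2 days.
- k = 6, d = 80, n = 87: 6 × 80 / 87 = 5.5 days. The false-claim risk at a true difference of 30 is P(Z > 1.96 − 5.5/12.1) = P(Z > 1.505), about 6.6 %. The same 5.5 days with a standard error of 13.2 gives about 6.2 %.
- k = 3, d = 80, or k = 6, d = 40: 240 / 87 = 2.8 days, risk about 4.2 %.
- k = 1, d = 80: 80 / 87 = 0.9 days, risk about 3.0 %.

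**Timing.** The article appeared on 28 July 2015 and recruitment was to run to the end of August 2016 (Trial status). The block size was therefore public for about 13 months of planned enrolment.

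**The case against.** The best defence is that the envelopes are opaque and sealed, so a blind pick is itself a random act. In the in-person route the patient chooses, not the staff. The statistician's table still fixes the envelope contents. Eligibility and written consent precede allocation in both routes, so an opened envelope cannot drive an exclusion. The rehabilitation physician decides on eligibility (Recruitment of participants), not the screening team alone. Queueing patients is hard: 115 a year over 16 cells is about 7 per cell per year, or one every seven weeks or so. Stratification also limits steering on sick-leave duration and type.

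Most of this stands, and it rules out several stronger readings that a reader might infer:

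- *Picking from two makes allocation predictable.* It does not. Predictability comes from the small fixed blocks.
- *The allocation cannot be audited.* In person, the patient signs a note from a coded envelope, which is a record of a kind. The narrower statement holds: the numbering cannot show out-of-order use when that is the procedure.
- *Staff choose one of two envelopes in telephone cases.* The article says only that they allocate without the patient. The choice is an inference, although no other procedure is described.
- *Screening staff know the block size and see all earlier allocations in their cell.* The article neither says so nor rules it out.

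The defence does not restore the sequence, give the telephone route a rule, or prevent anticipation before consent.

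**Conclusion.** The point holds as two separate weaknesses. First, the pick of two means that the numbered sequence no longer determines allocation, and the telephone route leaves an unblinded team member without a stated envelope rule. Nothing else in the article repairs either gap. Second, fixed, published blocks of four in 16 small cells let an observer be certain of 1/3 of allocations and guess 70.8 % correctly, provided that the observer knows the size and tracks the cell and that blocks are used in order.

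The documents give no basis for saying that steering occurred, in which direction, or how large a bias would be. Steering harder cases to 40-h would work against a non-inferiority claim. The 5.5-day shift and the 6–7 % risk rest on an assumed number of patients and an assumed difference of one SD, and smaller assumptions give smaller effects. They show only that a handful of patients could matter against a nominal 2.5 %. The change is worth making because it is cheap and the trial has no blinding to fall back on.

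**What to change.** For patients still to be enrolled:

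1. Drop the pick of two. After eligibility and consent are recorded, open only the lowest-numbered unused envelope of the stratum, with participant code and date written on it first. Apply the same rule to telephone cases.
2. Preferably, let the independent researcher who already holds the coding scheme (Blinding) release the next allocation, so that the screening team does not handle the envelopes.
3. Issue a new list with randomly varying block sizes that are not disclosed to the centres.

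Step 1 alone takes off-sequence allocation from about 63–73 % to 0 % but leaves the 1/3 and 70.8 % as they are, so step 3 is also needed. The gain from step 3 should not be oversold. With blocks of 2, 4 and 6 mixed at random, guessing from the running imbalance still succeeds in 69.3 % of cases by simulation. The benefit is that an observer who does not know the sizes can no longer be certain of an allocation by counting to four.

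The cost is a short amendment, a new list, and a brief wait for release if step 2 is adopted. Patients already enrolled are not covered, so the report should say how many were allocated under each procedure.

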### Blinding

Blinding in this study is not possible because of the nature of the intervention. However, the data analyst will remain blinded to the allocation. Participants will complete self-reported web-based questionnaires outside the study setting, so the multidisciplinary intervention team has no influence on the outcome assessment. After randomization, all participants are labelled with a research code consisting of a unique consecutive number. An independent researcher will maintain the coding scheme. Data analysis will be performed using this research code to guarantee that analyses of the data by the researcher will be blinded.

### Co-interventions and compliance

The patients’ self-reported healthcare usage data will be used for the assessment of co-interventions. Compliance will be assessed using information about attendance to the program and compliance to the treatment protocol and will be assessed after each intervention session in an electronic log by a member of the multidisciplinary intervention team (MIT). Furthermore, the MIT member will determine at discharge if the program was completed as planned. This will be assessed on a binary scale: “program completed as planned,” or “program deviated.” In the latter case, a closed question follows: program deviated due to “early discontinuation due to adverse events such as accident, surgery, or major private event,” “early discontinuation due to goals being achieved,” “extension of intervention program due to non-achievement of goals,” or “other reasons.” In the case of an early discontinuation or extension of the program, the number of deviated weeks will be reported. The information about compliance will be applied to perform the per protocol analyses.

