**Methods/Design:**

A non-inferiority study design will be applied. The study population consists of workers who are on part-time or full-time sick leave due to subacute or chronic nonspecific musculoskeletal pain. Two multidisciplinary vocational rehabilitation programs following the bio-psychosocial approach will be evaluated in this study: 40-h vocational rehabilitation and 100-h vocational rehabilitation, both delivered over a maximum of 15 weeks. The 100-h vocational rehabilitation comprises five modules: work participation coordination, graded activity, cognitive behavioral therapy, group education, and relaxation. The 40-h vocational rehabilitation comprises work participation coordination and a well-reasoned choice from the other four modules. Four rehabilitation centers will participate in this study, each delivering both interventions. Patients will be randomized into one of the interventions, stratified for the duration of sick leave (<6 weeks or ≥6 weeks) and type of sick leave (part-time or full-time). The primary outcome is work participation, measured by self-reported sick leave days, and will be assessed at baseline, mid-term, discharge, and at 2, 4, 6, 8, 10, and 12 months follow-up. Secondary outcomes are work ability, disability, quality of life, and physical functioning and will be assessed at baseline, discharge, and at 6 and 12 months follow-up. Cost outcomes are absenteeism, presenteeism, healthcare usage, and travelling costs. Cost-effectiveness will be evaluated from the societal and employer perspectives.

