### Data collection

Self-reported data will be collected using web-based questionnaires. Data will be collected at baseline (that is, before and during the multidisciplinary screening, T0), 7 weeks after the start of the intervention (midterm, T1), 14 weeks after the start of the intervention (discharge, T2), and at 2, 4, 6, 8, 10 and 12 months follow-up after discharge (T3-T8). Figure 2 shows the timing of the data collection. In addition, pilot data show an expected delay of approximately 1.5 months between baseline and the start of the intervention. At each data point, participants will receive an email with login data and the request to complete questionnaires on a website. If participants do not complete the questionnaire within a week, they will receive a reminder email. If the questionnaire is not completed after this reminder, patients will be telephoned by a researcher (TB), who will ask patients to complete the questionnaire. Table 1 presents the outcome measures of the data collection.

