**Fig. 2 Fig2:**
[figure not shown]
Timing of data collection

**Table 1 Tab1:** Outcome measures for each of the measurement moments

Outcomes	Time measured			Follow-up					
	Baseline	Midterm	Discharge	2 months	4 months	6 months	8 months	10 months	12 months
	T0	T1	T2	T3	T4	T5	T6	T7	T8
Descriptive variables									
Demographic variables	x								
General perceived health	x								
Work-related psychosocial factors	x								
Self-efficacy of work participation	x								
Pain intensity	x		x						
Fatigue	x								
Work tolerance functions	x								
Outcome measures									
Primary									
Work participation^a^	x	x	x	x	x	x	x	x	x
Secondary									
Work ability	x		x			x			x
Disability	x		x			x			x
Physical functioning	x		x			x			x
Quality of life	x		x			x			x
Costs^a^									
Presenteeism	x	x	x	x	x	x	x	x	x
Health care usage	x		x		x		x		x

^a^The primary outcome *work participation* will also serve as a cost outcome (that is, absenteeism)

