
#### Cost outcomes

The following outcomes will be assessed to evaluate the cost-effectiveness of the 40-h VR compared with the 100-h VR:Absenteeism data will be derived from the work participation (that is, primary outcome) data in this study.Presenteeism will be assessed using the presenteeism items of the iPCQ [34]. The questionnaire measures the total days of mental or physical complaints at work, with a recall period of 4 weeks. The amount of work performed accompanied by mental or physical complaints is measured on a 0 to 10 response scale, where 0 represents “I couldn’t do anything,” to 5 “I could do about half of normal,” to 10 “I could do the same as normal.” A population with mental health problems showed good feasibility and validity [34], and moderate reliability for the number of days while impeded by mental or physical complaints (icc 0.56), and a satisfactory reliability for the efficiency rate (0 to 10) item (icc 0.73) [36].Healthcare usage will be assessed using the Trimbos iMTA questionnaire for measuring Costs of Psychiatric Illnesses (TiC-P), module 1 [36, 44]. A recall period of 4 weeks is used in this questionnaire. Visits and consultations of the following healthcare providers were measured: general practitioner, physiotherapist, manual therapist, exercise therapist, occupational therapist, psychologist, insurance physician, medical specialists in hospitals, hospitalization (number of days), occupational physician, social worker, and dietician. Additional items were alternative care, home care, medication use, and job-related care like job coaches, ergonomic changes at the work site and reintegration specialists. Slight adaptations in the context and scope of health care practitioners were made to better match TiC-P to the target population (that is, from psychiatry to pain and work). Another modification was that visits and consultations were measured in both generic and sickness-specific terms. Research shows that health care usage assessment by means of self-reported questionnaires is reliable [45]. A population with mental health problems showed good feasibility, promising construct validity, good agreement on medical resource use (yes/no), and sufficient test-retest reliability on the number of contacts with the health care providers [36]. Until now, reliability of the TiC-P has not been tested in our study population. This needs to be done in the near future.

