### Strengths and limitations of this study

The first strength of this study is the assessment of the primary outcome work participation with self-reported questionnaires with a recall period of one month. This recall period will prevent recall bias. In addition, self-reported data about work participation has been shown to be a reliable alternative compared with electronic databases [67]. The second strength of this study is the analysis of the cost-effectiveness from both the societal and the employer’s perspective. It is important to provide employers with information on the return on investment of both interventions, as this will help them to consider the right treatment. A third strength of this study is that we consider presenteeism in the cost-effectiveness evaluation. Although most cost-effectiveness studies do not assess presenteeism [17, 18, 31, 35, 68], it is meaningful to take into account since the costs related to it are enormous, as shown by Lötters et al. [69], who found that for workers who returned to work after musculoskeletal disorders, the median loss for an 8-h workday was 1.6 h, and this remained at 12-month follow-up. A final strength of this study is the participation of four rehabilitation centers, all working with the bio-psychosocial model as a blueprint. This will increase the generalizability of this study.

A limitation of this study is that it is not possible to blind the patients and the multidisciplinary intervention and screening team. This may result in non-compliance to the treatment protocol, because patients may be aware of which intervention parts they do not receive (especially in the 40-h VR group), whereas other patients in the same group will receive all intervention modules (see Appendix 1). When this deviation occurs on a large scale in the 40-h VR group, this will harm conclusions about non-inferiority. Another limitation of this study is that we do not correct for compensation costs, that is, when colleagues take over the work of the less productive employee in their regular working hours. This may overestimate presenteeism costs [70].

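### Outside care in programme weeks 1-10 falls in no recall window, because the healthcare-usage questionnaire is not asked at midterm

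*Protocol article*

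**What the plan says.** The section Co-interventions and compliance states that "self-reported healthcare usage data will be used for the assessment of co-interventions". The electronic session log in the same section records attendance and adherence to the programme, not care obtained elsewhere.

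Of the healthcare-usage questionnaire, Cost outcomes says: "A recall period of 4 weeks is used in this questionnaire". It covers, among others, physiotherapist, exercise therapist and psychologist contacts. In Table 1 the row "Health care usage" is marked at T0, T2, T4, T6 and T8. It is blank at T1, where sick leave and presenteeism are both marked.

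Data collection places T1 at "7 weeks after the start of the intervention (midterm, T1") and T2 at "14 weeks after the start of the intervention (discharge, T2"). Baseline is taken before and during the screening, and the Randomization section places allocation after it. Data collection adds that "pilot data show an expected delay of approximately 1.5 months between baseline and the start of the intervention".

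The societal cost-effectiveness analysis counts healthcare use among the direct medical costs. The Effectiveness section specifies linear extrapolation between time points for sick leave. The article states no such rule for healthcare use.

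**The concern.** The trial compares two doses of rehabilitation. If patients in the 40-h arm obtained physiotherapy or psychology elsewhere during the programme, the treatment received would differ by less than the nominal 60 h, and that outside care would have a cost. The only instrument that could show this looks back over the last four programme weeks. The measurement before it was taken before allocation, so it carries no information on an arm difference.

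Two uses of the data are affected. The first is interpretation: under Implications for practice, the article promises knowledge of the dose-effect relation, which requires the dose received to be known. The second is the societal cost comparison, where healthcare use in weeks 1-10 can enter only through an extrapolation that the article does not describe. The schedule itself is fixed in this document, and no later analysis rule can recover care that was never asked about.

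**Working it through.** **Inputs.** Recall 4 weeks (Cost outcomes). Healthcare use at T0, T2, T4, T6, T8 (Table 1). T1 at week 7, T2 at week 14, T0 about 1.5 months before start (Data collection); 6.5 weeks is assumed. Session schedules from the Interventions section: 40-h arm two per week in weeks 1-5, one per week in weeks 6-10, 2-3 in total in weeks 11-15; 100-h arm two per week for 15 weeks.

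**The 60 h contrast reproduces.** Appendix 1 gives 10 + 60 + 7.5 + 15 + 7.5 = 100 h. The 40-h programme is 10 + 30 = 40 h. The difference is 60 h.

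**Coverage.** The T2 window is weeks 11-14: 4/14 = 29 %. Since the programmes are "both delivered over a maximum of 15 weeks", the figure at the maximum length is 4/15 = 27 %. Weeks 1-10 (10/14 = 71 %) lie in no window. From start to T8, healthcare use has 4 windows × 4 weeks = 16 of about 66 weeks (24 %); sick leave has 8 × 4 = 32 of 66 (48 %).

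**Effect of linear filling from T0 (assumed rule).** At week t the filled value gives T2 the weight (t + 6.5)/20.5. Averaged over t = 0 to 14 this is (6.5/20.5 + 1)/2 = 0.66, leaving 0.34 on T0. The expected arm difference at T0 is zero.

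- *Constant arm difference:* 66 % is captured, so it is understated by 34 %.
- *Arm difference follows the shortfall in hours.* Assume equal session length within each arm and 2.5 sessions in weeks 11-15, so 17.5 sessions of 40/17.5 = 2.29 h, against 100/15 = 6.67 h per week. The weekly shortfall is 6.67 − 4.57 = 2.10 h (weeks 1-5), 6.67 − 2.29 = 4.38 h (weeks 6-10) and 6.67 − 1.14 = 5.52 h (weeks 11-15). The true mean over weeks 1-14 is (5 × 2.10 + 5 × 4.38 + 4 × 5.52)/14 = 3.89. The filled mean is 0.66 × 5.52 = 3.64. The ratio is 0.93, so the understatement is about 7 % (3 % with 2 late sessions, 10 % with 3).
- *Arm difference follows the shortfall in session counts* (0, 1 and 1.5 per week): true mean (0 + 5 + 6)/14 = 0.79, filled 0.66 × 1.5 = 0.99, so it is overstated by about 26 %.
- *Use confined to weeks 1-10:* the T2 difference is zero, so none is captured.

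**Other rules.** For a constant difference, no filling captures 29 %, and carrying the T2 rate back over the interval captures 100 %.

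**With the module added at T1.** The windows become weeks 4-7 and 11-14: 8/14 = 57 %. Take the T1 rate for weeks 1-7 and a line from T1 to T2 for weeks 8-14. A constant difference is then recovered in full. For the hours pattern, T1 records (2 × 2.10 + 2 × 4.38)/4 = 3.24, and the total is 7 × 3.24 + 7 × (3.24 + 5.52)/2 = 53.3 against a true 54.5, or 2 % low. For the session-count pattern it is 7 × 0.5 + 7 × 1.0 = 10.5 against 11, or 5 % low.

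**The case against.** The strongest objection is that the window sits where it matters most. Both arms have two sessions per week in weeks 1-5, and the gap widens later, so weeks 11-14 hold about 36-38 % of the missing hours and 47-49 % of the missing sessions. This stands. It refutes any claim that weeks 1-10 are the likeliest time for substitution, but it still leaves more than 60 % of the missing hours outside the window.

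A reader might infer that outside care goes uncosted. That does not follow: healthcare use is a cost item, and the filling rule may be in the full protocol or analysis plan. How much is captured depends on that rule and on the time pattern of use.

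A reader might also take the article's remark that "patients may be aware of which intervention parts they do not receive (especially in the 40-h VR group") as a prediction that patients will seek therapy elsewhere. In context it concerns non-compliance within the programme, which the session log and the discharge assessment address. No passage says that patients will obtain outside care.

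Nor does the gap undermine the primary test. The intention-to-treat analysis compares the programmes as randomised, and no planned analysis adjusts for co-interventions. Care after discharge is sampled at T4, T6 and T8.

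What none of this answers is that the sole monitor of co-interventions skips an existing questionnaire at week 7, so the trial could not tell whether early substitution took place.

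**Conclusion.** The point holds as a gap in measurement. Outside care in weeks 1-10 of 14 is not directly observed, and the anchor before the discharge window predates randomisation.

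The size of any cost error is not fixed by the documents. It rests on three assumptions: linear filling from T0, a T0 about 6.5 weeks before start, and no arm difference at T0. Under these, the understatement is about 34 % for a constant arm difference and about 7 % if outside use tracks the shortfall in hours. A pattern tracking session counts would be overstated instead, so even the direction depends on an unknown pattern. Use that stops before week 11 is missed.

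The consequence is limited to the societal costs and to interpreting the result as a comparison of doses. The non-inferiority test under intention to treat remains valid.

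**What to change.** 1. In Table 1, add the existing healthcare-usage module at T1 with its 4-week recall unchanged. Enrolment began in November 2014, so this applies only to patients not yet past T1.
2. Where T1 is available, cost the programme period from T1 and T2 rather than from the pre-randomisation T0 value, and state the filling rule, for example the one in the working above.
3. Report outside physiotherapy, exercise therapy and psychology contacts during the programme by arm, beside the primary result.

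The cost is a few more minutes per patient in a web questionnaire that is already sent. Weeks 1-3 and 8-10 stay unobserved. A longer recall would close them, but it would make these windows inconsistent with the other time points and weaken recall, so it is not recommended here.
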